#### **6.3.2.3 Visit 7 (Week 4) and 9 (Week 8)**

The subject will receive 2 further investigational vaccinations/placebos in 4 weekly intervals at Visit 7 and 9 according to the assigned randomisation schedule. The following procedures will be performed prior to the administration of the investigational vaccination/placebo:

- A symptom directed physical examination (see Section 6.4.2);
- Vital signs(see Section 6.4.3);
- Urine samples for urinalysis and pregnancy testing (see Section 6.4.5 and 6.4.6);
- Blood samples for:
  - Haematology (see Section 6.4.5);
  - Clinical chemistry (see Section 6.4.5);
- Blood samples for immunological assessments including:
  - ELISA (anti HSV-2 gD2 antibodies) (see Section 6.4.5);

The investigational vaccination/placebo will be administered and the resultant bleb will be inspected. The results of the bleb inspection will be recorded in the source documents.

Vital signs will be measured at 30 and 60 minutes following the administration of the investigational vaccine/placebo. Subjects will be observed during this time.

The subject will be issued with an Injection Site Reaction Diary and instructed to view their injection site(s) at the same time each day and record their findings every day for 7 days.

#### **6.3.2.4 Visit 10 / Week 8 + 48 hours**

Visit 10 is to be scheduled for all subjects 48 hours after receiving their third vaccination at Visit 8. There is a +/- 12 hour window for this visit.

All subjects will have their injection sites assessed by the Investigator or designee. Any reactions will be recorded in the source notes and the corresponding CRF page. All subjects regardless of whether they have had an injection site reaction will have a photograph taken in a standardised manner. Please refer to Section 6.4.8.

A symptom directed physical examination will be performed (see Section 6.4.2).

Skin biopsies will be taken from all subjects who provide consent at their injection sites. Please refer to Section 6.4.11.

Adverse event, occurrences of HSV-2 outbreaks and concurrent medication questioning will occur (see Section 7 and 8).

The Injection Site Reaction Diary will be reviewed and returned to the subject.

#### **6.3.2.5 Visit 11 / Week 9**

Visit 11 will take place one week after the third investigational vaccination/placebo. The following procedures will be performed:

- Symptom directed physical examination (see Section 6.4.2);
- Review and collection of the Injection Site Reaction Diary (see Section 6.4.11);
- Adverse event, occurrences of HSV-2 outbreaks and concurrent medication questioning (see Sections 7 and 8);
- Blood samples for:
  - Haematology (see Section 6.4.5);
  - Clinical chemistry (see Section 6.4.5);
- Blood samples for immunological assessments including:
  - ELISpot (T-cell responses specific for HSV-2 gD2) (see Section 6.4.5);
  - Exploratory Immune assays (see Section 6.4.5);
- If the subject has evidence of a hypersensitivity type reaction at their injection site(s) photographs will be taken in a standardized manner (see Section 6.4.8).

The subject's will receive refresher training on the swabbing collection procedure, HSV-2 Symptoms and Swabbing Diary completion and HSV-2 outbreak management. The Post Vaccination Shedding Assessment will commence on the day of Visit 11 in the clinic under supervision. Subjects will be encouraged to collect swabs at the same time each day for 45 days. Subjects will also be required to complete the HSV-2 Symptoms and Swabbing Diary each day of the shedding assessment to record any HSV-2 symptoms that occur. (See sections 6.4.9 – 6.4.10 and 9).

The subject will be issued with:

- Swabbing materials, and
- HSV-2 Symptoms and Swabbing Diary.

#### **6.3.2.6 Visit 12 / Week 12**

Visit 12 will be scheduled 4 weeks after the third vaccination. The following procedures will be performed:

- Symptom directed physical examination (see Section 6.4.2);
- Vital signs (see Section 6.4.3);
- Blood samples for:
  - Haematology (see Section 6.4.5);
  - Clinical chemistry (see Section 6.4.5);

- Blood samples for immunological assessments including:
  - ELISA (anti HSV-2 gD2 antibodies) (see Section 6.4.5)
- Review of the HSV-2 Symptoms and Swabbing Diary (see Section 6.4.10); and
- Adverse event, occurrences of HSV-2 outbreaks and concurrent medication questioning (see Sections 6.4.10, 7 and 8).

The subject's will receive refresher training on the swabbing collection procedure, diary completion and HSV-2 outbreak management.

#### **6.3.2.7 Visit 13 / Week 15**

Visit 13 will be scheduled 45 days after Visit 10 at the end of the Post Vaccination Shedding Assessment.

The following procedures will be performed:

- Symptom directed physical examination (see Section 6.4.2)
- Review and collection of the HSV-2 Symptoms and Swabbing Diary (see Section 6.4.10); and
- Adverse event, occurrences of HSV-2 outbreaks and concurrent medication questioning (see Sections 6.4.10, 7 and 8);

#### **6.3.2.8 At Visit 14 / Week 19**

The subject will be contacted via the phone at Week 19. Adverse event, the occurrence of HSV-2 outbreaks and concurrent medication questioning will take place. Subjects will be reminded about their next scheduled appointment.

### **6.3.3 Study Period 2 (Booster injection)**

#### **6.3.3.1 At Visit 15 / Week 23**

Visit 15 is a clinic visit and will take place one week prior to the Booster investigational vaccination/placebo. The following procedures will take place:

- Symptom directed physical examination (see Section 6.4.2);
- Collection of blood samples for:
  - Haematology (see Section 6.4.5);
  - Clinical chemistry (see Section 6.4.5);
- Adverse event, occurrences of HSV-2 outbreaks and concurrent medication questioning (see Section 6.4.10, 7 and 8).

#### **6.3.3.2 At Visit 16 / Week 24**

The subject will receive the Booster investigational vaccination(s)/placebo at Week 24 following the completion of the safety assessment procedures including:

- A symptom directed physical examination (see Section 6.4.2);
- Vital signs(see Section 6.4.3);
- Adverse event, occurrences of HSV-2 outbreaks and concurrent medication questioning (see Sections 6.4.10, 7 and 8);
- Blood samples for:
  - Haematology (see Section 6.4.5);

- Clinical chemistry (see Section 6.4.5);
- Blood samples for immunological assessments including:
  - ELISpot (T-cell responses specific for HSV-2 gD2) (see Section 6.4.5);
  - Exploratory Immune assays (see Section 6.4.5)
  - ELISA (anti HSV-2 gD2 antibodies) (see Section 6.4.5)
- Urine samples for urinalysis and pregnancy testing (see Section 6.4.5 and 6.4.6);

The investigational vaccination/placebo will be administered and the resultant bleb will be inspected. The results of the bleb inspection will be recorded in the source documents.

Vital signs will be measured at 30 and 60 minutes following the administration of the investigational vaccine/placebo. Subjects will be observed during this time.

The subject will be issued with an Injection Site Reaction Diary and instructed to view their injection site(s) at the same time each day and record their findings every day for 7 days.

#### **6.3.3.3 At Visit 17 / Week 25**

Visit 17 will take place one week after the Booster investigational vaccine/placebo. The following procedures will be performed:

- Symptom directed physical examination (see Section 6.4.2);
- Review and collection of the Injection Site Reaction Diary (see Section 6.4.10);
- Collection of blood samples for:
  - Haematology (see Section 6.4.5);
  - Clinical chemistry (see Section 6.4.5);
  - ELISpot (T-cell responses specific for HSV-2 gD2) (see Section 6.4.5);
  - Exploratory Immune assays (see Section 6.4.5);
- Adverse event, occurrences of HSV-2 outbreaks and concurrent medication questioning (see Sections 6.4.10, 7 and 8);
- If the subject has evidence of a hypersensitivity type reaction at their injection site(s) photographs will be taken in a standardized manner (see Section 6.4.8).

The subject's will receive refresher training on the swabbing collection procedure, HSV-2 Symptoms and Swabbing Diary completion and HSV-2 outbreak management. The Post Booster Vaccination Shedding Assessment will commence on the day of Visit 17 in the clinic under supervision. Subjects will be encouraged to collect swabs at the same time each day where possible for 45 days. Subjects will also be required to complete the HSV-2 Symptoms and Swabbing Diary each day of the shedding assessment to record any HSV-2 symptoms that occur. (See sections 6.4.9 – 6.4.8 and 9).

#### **6.3.3.4 At Visit 18 / Week 28**

Visit 18 will be scheduled 4 weeks after the booster vaccination. The following procedures will be performed:

- Symptom directed physical examination (see Section 6.4.2);
- Vital signs (see Section 6.4.3);
- Collection of blood samples for:
  - Haematology (see Section 6.4.5);
  - Clinical chemistry (see Section 6.4.5);
- Blood samples for immunological assessments including:
  - ELISA (anti HSV-2 gD2 antibodies) (see Section 6.4.5);
- Review of the HSV-2 Symptoms and Swabbing Diary (see Section 6.4.10); and
- Adverse event, occurrences of HSV-2 outbreaks and concurrent medication questioning (see Sections 6.4.10, 7 and 8).

The subject's will receive refresher training on the swabbing collection procedure, HSV-2 Symptoms and Swabbing Diary completion and HSV-2 outbreak management.

#### **6.3.3.5 At Visit 19 / Week 31**

The subject will return to the clinic for Visit 19 will be scheduled 45 days after Visit 17 after completing the Post Booster Shedding Assessment.

The following procedures will be performed:

- Symptom directed physical examination (see Section 6.4.2);
- Review and collection of the HSV-2 Symptoms and Swabbing Diary (see Section 6.4.10); and
- Adverse event, occurrences of HSV-2 outbreaks and concurrent medication questioning (see Sections 6.4.10, 7 and 8).

#### **6.3.4 Follow up**

##### **6.3.4.1 Visit 20 / Week 36 and Visit 21 / Week 42**

At Visit 20 and Visit 21, the site staff will telephone the subject and collect the following information:

- Adverse event, occurrences of HSV-2 outbreaks and concurrent medication questioning will occur. (See Sections 6.4.10, 7 and 8).

##### **6.3.4.2 Visit 22 / Week 48 / End of Study (or early withdrawal from treatment visit)**

The end of study visit will be conducted in the clinic. The following tests will be performed and documented as indicated on the CRF:

- Symptom directed physical examination (see Section 6.4.2);
- Vital signs (see Section 6.4.3);
- Adverse event, occurrences of HSV-2 outbreaks and concurrent medication questioning (see Sections 6.4.10, 7 and 8);
- Blood samples for
  - Haematology (see Section 6.4.5);
  - Clinical chemistry (see Section 6.4.5);
- Blood samples for immunological assessments including:
  - ELISpot (T cell responses specific for HSV-2 gD2) (see Section 6.4.5);
  - Exploratory Immune assays (see Section 6.4.5)
  - ELISA (anti HSV-2 gD2 antibodies) (see Section 6.4.5)
- Urine samples for urinalysis and pregnancy (see Sections 5 and 6.4.6)

#### **6.4 Details of Scheduled Assessments**

##### **6.4.1 Demographic Data, Medical/Surgical History, Medication History and Concurrent Medication**

Demographic data will include gender, ethnicity and date of birth.

The medical history will include any diagnosed medical conditions or surgical history. It will also include the existence of any birthmarks, tattoos, wounds or other skin conditions on the forearms.

Where possible, subjects will be asked to provide documented evidence from their local doctor that they have a diagnosis of HSV-2 and details regarding their HSV-2 outbreak recurrence history.

All genital herpes medication history, and concurrent medication, including non-prescription medication, will be collected and recorded in the CRF.

### 6.4.2 Physical examination

A complete physical examination (including head, ears, nose, throat, lungs, lymph nodes, heart, abdomen, skin and genital region) will be conducted to determine study eligibility at screening. A symptom directed physical examination will be performed at subsequent visits as defined in Section 6.3. The symptom directed physical examinations will be performed based on signs and symptom the subject has reported verbally and/or documented in the diary booklets. A symptom directed physical examination may also be performed if in the opinion of the Investigator it is required.

Prior to each injection, the forearm that is to be injected will be examined and findings from this examination will be documented.

At each visit, following Visit 5, the subject's injection sites will be inspected and any reactions will be graded. Please refer to Section 8. Any reactions should also be captured as adverse events within the CRF.

### 6.4.3 Vital signs

Vital signs to be measured are:

- body temperature (degrees Celsius) aural;
- respiratory rate;
- pulse rate;
- blood pressure; and
- Height and body weight will be measured and documented at the Screening visit.

Vital signs will be measured after the subject has been in a resting semi- supine position for at least 3 minutes. If there are abnormalities, at least two further repeat BP measurements will be performed to confirm results. On visits where the subject is scheduled to receive a vaccination, the vital signs must be performed prior to receiving the investigational vaccine. If the subject's temperature is > 38 degrees Celsius, the investigational product will be withheld for up to one week. Please see Section 8.6.

On dosing days, vital signs will also be performed at 30 and 60 minutes post dosing.

Body weight (kilogram [kg], without shoes), and Height (centimetres [cm], without shoes) will be measured and documented at the Screening visit.

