A total of 143 local ADRs were reported during the study period by 21 subjects (95.5%). The number of local ADRs reported increased with increasing dose of COR-1. Erythema and induration were the most frequently reported injection site reactions, occurring in at least one subject in each treatment group at some point during the vaccination phase. Erythema was reported more frequently in the 100 mcg, 300 mcg and 1 mg COR-1 treatment groups. Induration was reported more frequently in the 1 mg COR-1 treatment group. All injection site reactions were classified as mild in intensity.

A total of 14 systemic ADRs were reported during the study period by four subjects (18.2%). The most frequently reported were headache, fatigue, chills, malaise, pain and pyrexia. There were no trends in the frequency of systemic ADRs by treatment group. All the systemic ADRs reported were classified as mild in severity.

Review of haematology and biochemistry results revealed no trends or notable changes over time following vaccination with COR-1 at any dose level. There were no trends or notable findings in vital signs following each vaccination with COR-1 at any dose level.

A review of the safety data suggests that 3 ID vaccinations of the COR-1 vaccine at three weekly intervals were safe and well tolerated.

No anti-HSV gD2 antibodies were detected in any subject by ELISA, indicating that no subjects had seroconverted to COR-1 during the study based on the utilised method.

IFN- $\gamma$  production by T cells specific for gD2 antigen was induced in 19 of the 20 subjects who completed the study as planned and was considered a cell-mediated response to the COR-1 vaccine. The response rates were similar in all treatment groups with 100.0% of subjects responding to the COR-1 vaccine in the 10 mcg, 30 mcg, 300 mcg and 1 mg groups and 75.0% responding in the 100 mcg group.

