### 4.2 Endpoints

#### Primary endpoints:

The primary endpoints of this study are:

- Incidence and severity of adverse events in each treatment group, including vaccine related adverse events:
  - Incidence and severity of local reactions (soreness, redness, induration, ecchymosis, oedema, itching and paraesthesia) at the site of vaccination;
  - Incidence and severity of systemic reactions (fatigue, myalgia, malaise, fever, rigors, arthralgia, nausea, diarrhoea, light headedness, dizziness, hypersensitivity and headache).

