### 8.2.1 Assessment of AEs

All AEs will be assessed by the Investigator and recorded on the appropriate CRF page, including the date of onset and resolution, severity, relationship to investigational vaccine/placebo, outcome and action taken with study medication. See Appendix 2 for details of toxicity grade scales (TGS) relevant to vital signs, local reactions to injectable product, systemic signs and symptoms, systemic illness, and clinical laboratory adverse events.

In addition, injection site reactions will be graded by an Investigator or designee, according to severity. It is anticipated that the subjects may find it difficult to differentiate pain and tenderness (Norquist et. al. 2012). For this reason pain and tenderness have been combined with the following grading scale:

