**Contains Nonbinding Recommendations**

| Vital Signs *                  | Mild (Grade 1)        | Moderate(Grade 2)     | Severe (Grade 3)  | Potentially Life Threatening (Grade 4)          |
|---------------------------------------|------------------------------|------------------------------|--------------------------|--------------------------------------------------------|
| Fever (°C) **
(°F) **              | 38.0 – 38.4
100.4 – 101.1 | 38.5 – 38.9
101.2 – 102.0 | 39.0 – 40
102.1 – 104 | > 40
> 104                                          |
| Tachycardia - beats per minute        | 101 – 115                    | 116 – 130                    | > 130                    | ER visit or hospitalization for arrhythmia             |
| Bradycardia - beats per minute***     | 50 – 54                      | 45 – 49                      | < 45                     | ER visit or hospitalization for arrhythmia             |
| Hypertension (systolic) - mm Hg       | 141 – 150                    | 151 – 155                    | > 155                    | ER visit or hospitalization for malignant hypertension |
| Hypertension (diastolic) - mm Hg      | 91 – 95                      | 96 – 100                     | > 100                    | ER visit or hospitalization for malignant hypertension |
| Hypotension (systolic) – mm Hg        | 85 – 89                      | 80 – 84                      | < 80                     | ER visit or hospitalization for hypotensive shock      |
| Respiratory Rate – breaths per minute | 17 – 20                      | 21 – 25                      | > 25                     | Intubation                                             |

\* Subject should be at rest for all vital sign measurements.

\*\* Oral temperature; no recent hot or cold beverages or smoking.

\*\*\* When resting heart rate is between 60 – 100 beats per minute. Use clinical judgement when characterizing bradycardia among some healthy subject populations, for example, conditioned athletes.

| Systemic (General) | Mild (Grade 1)                                    | Moderate(Grade 2)                                                                 | Severe (Grade 3)                                                          | Potentially Life Threatening (Grade 4)     |

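### Fever is a primary systemic reaction graded in degrees, but no temperature is scheduled from 1 hour to about 4 weeks after any dose, so delayed fever rests on self-report and cannot be reliably placed on the Appendix 2 bands

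*Protocol*

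**What the plan says.** Section 4.2 includes in the primary endpoint "Incidence and severity of systemic reactions (fatigue, myalgia, malaise, fever, rigors, arthralgia, nausea, diarrhoea, light headedness, dizziness, hypersensitivity and headache", so fever is one of twelve listed systemic reactions, each to be described by incidence and severity.

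For grading, Section 8.2.1 directs: "See Appendix 2 for details of toxicity grade scales (TGS) relevant to vital signs, local reactions to injectable product, systemic signs and symptoms". The vital signs table in Appendix 2 grades fever by temperature alone: 38.0–38.4 °C is Grade 1, 38.5–38.9 °C Grade 2, 39.0–40 °C Grade 3, and above 40 °C Grade 4. Its footnote sets the route: "Oral temperature; no recent hot or cold beverages or smoking".

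For measurement, Section 6.4.3 lists "body temperature (degrees Celsius) aural", taken before each vaccination. It adds: "On dosing days, vital signs will also be performed at 30 and 60 minutes post dosing". The vital-signs rows of the two-part Table 1 are marked at Visits 1, 5, 7, 9, 12, 16, 18 and 22 only.

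For home recording, Section 6.4.10 describes the Injection Site Reaction Diary as covering pain/tenderness, swelling/induration, erythema and other findings for 7 days after each vaccination, with a ruler supplied. Note 7 to Table 1 and the synopsis also limit the 7-day record to injection site reactions. Section 8.2, however, says the diary booklets document solicited symptoms after vaccination, both local and systemic, and its list of systemic symptoms includes fever. None of these places mentions a thermometer or a temperature entry.

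**The concern.** A degree-based severity scale needs a temperature. If fever begins after the subject has left the clinic, the plan as written produces no scheduled reading to grade. What reaches the database then depends on whether the subject notices and reports it, and on whether anyone happens to take a temperature.

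Fever is a plausible reaction for this product. Section 3.2.4 says of the systemic reactions in Phase I: "The most frequently reported were headache, fatigue, chills, malaise, pain and pyrexia". Section 8.7 lists chills and pyrexia among the reactions expected here. Section 6.4.11 describes a local reaction that appears after 24 hours and is maximal at 48 hours, so the protocol itself expects vaccine reactions well beyond the first hour.

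The stake is the fever row of the primary safety description, in a trial with 30 COR-1 and 10 placebo subjects. The Safety Review Committee's review before the first booster would also lack scheduled temperatures from the reaction period. This is a matter of data collection, so no later analysis can recover readings that were not taken.

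**Working it through.** The plan states no figure on this point to reproduce. The check is a reading of the schedule plus simple arithmetic.

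**1. Interval from each dose to the next scheduled temperature after the 60-minute reading** (nominal visit times, Table 1):

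| Dose | Given at | Next visit with vital signs | Interval |
|---|---|---|---|
| 1 | Visit 5, Day 0 | Visit 7, Day 28 (pre-dose) | 28 − 0 = 28 days |
| 2 | Visit 7, Day 28 | Visit 9, Week 8 = Day 56 (pre-dose) | 56 − 28 = 28 days |
| 3 | Visit 9, Week 8 | Visit 12, Week 12 | 4 weeks = 28 days |
| Booster | Visit 16, Week 24 | Visit 18, Week 28 | 4 weeks = 28 days |

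The visit windows do not change the picture. With both windows at their extremes (±3 days, and ±7 days for Visit 5), the shortest interval is 28 − 7 − 3 = 18 days after dose 1 and 28 − 3 − 3 = 22 days after the others. All lie outside the 7-day diary period.

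**2. Clinic visits inside that gap.** Visit 10 (48 hours after dose 3) and Visits 6, 8, 11 and 17 (one week after each dose) have no mark in the vital-signs row. Their procedure lists in Sections 6.3.2.2, 6.3.2.4, 6.3.2.5 and 6.3.3.3 agree: each has a symptom-directed examination and adverse event questioning, but no vital signs.

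**3. Coverage of the diary week.** 7 days × 24 = 168 hours, and scheduled readings cover the first hour: 1 / 168 = 0.6%. There are no scheduled readings between 1 hour and 7 days after any of the four doses. This measures when temperature is looked at. It does not estimate how many fevers are missed.

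**4. The two severity scales can disagree.** Table 8 gives a functional grade for all other reported adverse events, while Section 8.2.1 refers vital signs and systemic signs to Appendix 2. A temperature of 39.2 °C that the subject tolerates easily is Grade 1 on Table 8 and Grade 3 on Appendix 2. Without a reading, only the functional scale can be applied. Section 8.6 keys its toxicity guidance to grade, so the difference reaches beyond a summary table.

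**5. Scale of the events concerned.** Phase I recorded 14 systemic reactions in 4 of 22 subjects: 4 / 22 = 18.2%. Assuming that rate for the 30 COR-1 subjects here, 30 × 0.182 ≈ 5.5 would have any systemic reaction. The number with pyrexia is not given. With expected counts this small, one or two fevers missed or wrongly graded would visibly change the description.

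**6. Route.** Clinic readings are aural and the bands are for oral temperature. The documents give no difference between the two, so it can be said that grades near a cut-point are uncertain, but not by how much.

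**The case against.** The strongest reply is that the protocol has several ways to capture fever. Section 8.2 treats it as a solicited systemic symptom and has the investigator grade diary entries for severity and causality. The diary booklets have room for adverse events (Section 6.4.10), and subjects carry an Observation Form that is reviewed at each clinic visit (Section 6.3.1.2). Adverse events are asked about at 48 hours after dose 3 and at one week after every dose. The symptom-directed examinations at those visits do not rule out taking a temperature. Unscheduled assessments are allowed (Section 6.3), and Table 8 supplies a defined functional grade. The diary form and the Study Reference Manual are not shown and might contain a temperature field. Phase I systemic reactions were all mild, with no trend by treatment group, and this is a descriptive pilot. Appendix 2 is nonbinding guidance that permits alternative approaches.

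Much of this stands. A reader might infer that vaccine fever cannot be measured or graded at all. The documents do not support that, because it can be reported, functionally graded, and measured at an unscheduled contact. A reader might also infer that the primary profile is biased towards no fever and hides a difference between COR-1 and placebo. That is not shown either: self-report without a reading can miss fever, but it can also record feeling feverish as fever. The aural route does not prevent grading.

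The reply does not supply a planned reading for delayed fever. Each route depends on the subject noticing and reporting it, and none is described as yielding a temperature. The protocol adopts the Appendix 2 scale in Section 8.2.1, so its nonbinding origin does not remove the mismatch.

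**Conclusion.** The point holds as a gap in measurement. For each of the four doses, no temperature is scheduled from 1 hour to a nominal 28 days afterwards, and the protocol describes no home recording. Delayed fever, a named part of the primary endpoint, therefore rests on self-report and a functional grade and cannot be reliably placed on the degree bands that Section 8.2.1 invokes. Two inconsistencies go with it: Section 6.4.10 against Section 8.2 on what the post-dose diary collects, and the aural route in Section 6.4.3 against the oral footnote in Appendix 2.

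The direction and size of any bias are not established. The conclusion assumes that the diary form and Study Reference Manual, which are not shown, add no temperature entry beyond what the protocol describes. If they do, the protocol text still needs to say so. The change is worth making because it is cheap and the missing readings cannot be recovered later.

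**What to change.** - Supply each subject with a thermometer at Visit 5. Add a daily temperature field, with the route of measurement, to the existing 7-day post-dose diary.
- Add a temperature reading at the existing Visit 10. Readings at the one-week visits would add little for fever in the first days and are not essential.
- State that solicited fever is graded from these readings on the Appendix 2 bands.
- Reconcile Section 6.4.10 (with note 7 to Table 1 and the synopsis) with Section 8.2 on whether the post-dose diary collects systemic symptoms.
- Reconcile the aural route in Section 6.4.3 with the oral footnote in Appendix 2. Clinic readings also feed the dosing-delay rule for temperatures above 38 °C (Sections 6.4.3 and 8.6), so this should be done without altering that rule.

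Cost: about 40 to 50 thermometers (40 subjects plus up to 10 replacements, Section 4.6), 7 × 4 = 28 diary lines per subject over the study, and one extra reading at Visit 10. No new visits or staff are needed, and the added burden on subjects is small.
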